### 5.3. Hypotheses

The group randomized to online vestibular rehabilitation will experience a greater and faster balance recovery measured with the VSS-SF compared with standard care.

## 6. Design of the clinical investigation

### 6.1. General information

This is a two-armed evaluator-blinded multicenter randomized controlled clinical trial investigating the effects of online vestibular rehabilitation compared with standard written instructions after acute onset vertigo. The standard care study arm will be granted access to the online rehabilitation tool at 3 months after enrollment.

## 6.2. Measurements to minimize bias

Subjects will be block-randomized (random blocksize of 4, 6 and 8) 1:1 using site-specific randomization lists generated in R. Randomization will be performed by an independent statistician at Registercentrum Norr. As a precaution measure the lists will contain 4 times as many posts as the expected number of participants at each site. The treatment allocation will be open to the participants and to the site study coordinators, however blinded primary endpoint assessments at week 6 by study coordinators from surrounding sites will be performed as detailed below (section 6.7).

To minimize the risk for an increased effect of rehabilitation mediated by the increased motivation stemming from participating in a clinical trial (in both study arms) the study nurses will be instructed to try to avoid acting as “coaches” and instead concentrate on data collection at the contacts with the participants. This way the effect in the intervention arm will be isolated to the vestibular rehabilitation app, and the effect in the control arm will be isolated to mimic current clinical practice.

Sites will differ according to patient base (e.g., ENT outpatient clinics vs stroke wards). This will entail site mediated differences in participant characteristics. Bias stemming from these differences will be mitigated by including a random effect for site in the primary outcome analysis, and by site stratified randomization.

## 6.3. Measurement of variables

The VSS-SF measures the frequency of 15 vestibular symptoms on a scale from 0 (no symptoms) to 4 (symptoms most days) during the past month. The score range is 0–60 and a difference from baseline of  $\geq 3$  points indicate a clinically significant change. The time frame (1 month) for the symptoms will be left as is for the evaluations at week 6 and after 3 months but for the baseline measurement the participants will be asked to report their symptoms during the last 24 hours; and the two response alternatives indicating the highest frequencies (3, quite often [every week] and 4, very often [almost every day]) will be modified to: 3, quite often (almost every hour) and 4, very often (almost all the time). Although this is a deviation from the original version of the VSS-SF this modification is necessary to capture the short-term status of participants soon after vertigo onset. The modified VSS-SF data will be used for the baseline symptom intensity assessments only.

The DHI (range 0–100 points, 0–30 mild, 31–60 moderate and  $\geq 61$  severe dizziness) investigates the effects of dizziness on everyday living. The between group mean DHI score will be compared at each time point as detailed in the statistics section. The scale has subcategories (physical, emotional and functional for DHI) and these will be analyzed separately as exploratory analyses although the total scores will be used for the secondary outcomes.

EQ-5D is an generic instrument which consists of five sub-domains (mobility, self-care, usual activities, pain/discomfort and anxiety/depression) with three severity levels (no, moderate and severe problems). For the current study, the Swedish version EQ-5D-3L will be applied, and the Swedish value set based on experienced health states will be applied to

obtain a health utility score in order to calculate quality-adjusted life years (QALYs). The UK MvH value set will be applied for sensitivity analyses.

The T25-FW data will be collected by using the mean (seconds) of two, timed attempts at walking a clearly marked 25-foot course.

Basic body sway data will be collected by using a locally developed application which utilizes cell phone built-in motion tracking. An enhanced gait analysis with a wearable motion tracking system will be performed at Umeå University Hospital for in-depth measurements.

The motion tracking and gait data consist of sagittal and frontal plane angles and angular velocities. The planes are plotted against each other, and large deviations (quartiles or standard deviations) indicate poor balance. An artificial intelligence paradigm to analyze gait recovery will also be explored.

The VOR gain in each subject is expressed as the mean of  $\geq 5$  approved impulses for each lateral canal (right, left); on an aggregated level expressed as the median of VOR means and the changes from baseline at 6 weeks and 3 months will be compared between the study arms (affected side).

BPPV will be investigated by asking questions regarding paroxysmal motion-dependent vertigo at 6 weeks and 3 months and performing dix-hallpike and head roll testing at 3 months.

#### 6.4. End of the clinical investigation

The clinical investigation ends when the last subject has completed the last follow-up. The sponsor will notify the Swedish Medical Products Agency within 15 days after the end of the clinical investigation.

#### 6.5. Comparator and supporting treatment.

The comparator (written instructions) is selected based on that the majority of participating sites uses this as a first line treatment for the target population. Furthermore, the alternative which would be physiotherapist led group training sessions, is not available or feasible to provide in a safe and cost-effective manner.

Swedish guidelines suggest a short-term oral corticosteroid treatment for those with vestibular neuritis although data to support positive long-term effects are lacking. All participants with a presumed vestibular neuritis (i.e. those with a uni-directional horizontal spontaneous or gaze-evoked nystagmus, a positive head impulse test to the opposite direction compared with the nystagmus and no other neurological symptoms or findings) will therefore be offered corticosteroid treatment; 50 mg oral prednisolone daily for 5 days, then taper during 5 days.

The comparator chosen in the study is written instructions for vestibular rehabilitation which is the method used by most participating site for the target population. No national guidelines or pre-existing decision support have been found to support how the target population should be handled and treated regarding vestibular rehabilitation.

## 6.6. Subjects

### 6.6.1. Inclusion criteria

To be included in the study, subjects must meet the following criteria:

- $\geq 18$  years old; *and*
- The subject has given written consent to participate in the study; *and*
- New acute onset dizziness or vertigo since  $\geq 24$  hours with pathological spontaneous or gaze-evoked nystagmus (i.e., an acute vestibular syndrome, AVS). The nystagmus as described above must be present at investigation between 24 hours and 7 days from onset, spontaneously, gaze-evoked or head-shake evoked and documented; *and*
- Screening and inclusion within 7 days of onset of continuous symptoms; *and*
- Symptomatic at inclusion

### 6.6.2. Exclusion criteria

Subjects must not be included in the study if any of the following criteria are met:

- Pre-existing vestibular disease or neurological disease anticipated to affect the ability to participate in the study or the effect of the intervention. N.B: Recurring AVS with no set diagnosis before inclusion is accepted, as is past transient neurological diseases such as TIA or migraine; *or*
- Inability to use the online rehabilitation tool, e.g., due to not having access to a computer, tablet or smartphone, not having access to the internet or lacking in experience with such tools; *or*
- Mental inability, reluctance or language difficulties that result in difficulty understanding the meaning of study participation; *or*
- Medical and/or physical contraindications to making the required head movements (e.g., vertebral dissection) or otherwise participating in the training and testing exercises or data collection; *or*
- Medication or other substance intake which can affect the ability to participate in the study or the reliability of the measurement methods. These medications include regular use of: Anticonvulsants, antiemetics/motion sickness medications, benzodiazepines, neuroleptics. Transient corticosteroid and/or antiemetic treatment related to the current vertigo is accepted.

### 6.6.3. Criteria and procedures for subject withdrawal or discontinuation.

If a subject experiences recurrence of an acute vestibular syndrome within 6 weeks from inclusion the subjects' participation in the study is to be discontinued. The reason for discontinuation is documented in the trial termination form in the eCRF system and any further data collection will be stopped.

If inability to continue study participation (follow up, data collection) due to physical, mental or technical issues arises the site PI is to be immediately notified. The trial termination form in the eCRF system is used to document the reason(s) for and date of discontinuation.

If inability to continue study participation (training) due to physical, mental or technical issues arises the participant will be asked to continue to participate for data collection and observation (ITT analysis).

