| Compare the effect of online vestibular rehabilitation with standard written instructions after acute onset vertigo on vestibular symptoms (superiority).                                                                                                                                                                                                                                                                                                                                                                                                                                                                                                                                                                                                                                                                                                                                                                                                                                                                                                                                                                                                                                                                                                                                   | The vertigo symptom scale short form (VSS-SF) score at 6 weeks after vertigo onset.                                                                                                                                                                                                                                                                                                                                                                                                                                                                                                                                                                                                                                                                                                                                                                                                                                                                                                                                                                                                                                                                                                                                                 |

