## 9. Statistical considerations

### 9.1. Analysis population

The primary analysis will be performed using the intention to treat cohort on both primary and secondary outcomes. Per protocol analyses will also be performed as part of the sensitivity analysis.

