## 9.9. Missing data

To preserve the ITT principle for the primary endpoint we will use, hierarchically, (1) the 6 weeks assessment of VSS-SF; if missing, (2) the 3 weeks assessment; and (3) the 3 months assessment. A sensitivity analysis will be performed by comparing the primary analysis results with and without the imputed values from the 3 weeks and 3 months values.

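### Stopping all data collection when acute vestibular syndrome recurs within 6 weeks conflicts with the intention-to-treat analysis and leaves the primary endpoint missing or substituted for these participants

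*Protocol*

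**What the plan says.** Section 6.6.3 of the protocol holds two follow-up rules that point in opposite directions.

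- After recurrence: "If a subject experiences recurrence of an acute vestibular syndrome within 6 weeks from inclusion the subjects' participation in the study is to be discontinued". It goes on: "The reason for discontinuation is documented in the trial termination form in the eCRF system and any further data collection will be stopped". The section does not define a recurrence or say who decides that one has occurred.
- After inability to train: "the participant will be asked to continue to participate for data collection and observation (ITT analysis").

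Section 9.1 sets the population: "The primary analysis will be performed using the intention to treat cohort on both primary and secondary outcomes". The list of abbreviations explains intention to treat as using every participant's data. The primary endpoint in 5.2 is "The vertigo symptom scale short form (VSS-SF) score at 6 weeks after vertigo onset".

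Section 9.9 gives a substitution order, expressly to protect intention to treat for the primary endpoint. The week-6 score comes first; "if missing, (2) the 3 weeks assessment" is used; the 3-month score comes last. A sensitivity analysis with and without the substituted values is planned.

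**The concern.** Recurrence happens after randomisation and inside the period that the primary endpoint assesses. The VSS-SF counts how often 15 vestibular symptoms occurred over the preceding month (6.3), so a recurrence is close to being an outcome in itself. Ending measurement at that moment makes missingness depend on the outcome, and possibly on the arm.

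Recurrence is foreseeable, because 6.6.2 admits people with recurring AVS that had no set diagnosis before inclusion. The trial is described as pivotal and confirmatory (3.3) and passes or fails on a difference of at least 3 points (9.5), so a modest shift near that line matters. The stop also loses the 3-month and 12-month outcomes and the falls and fractures endpoint for these participants.

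**Working it through.** **1. What the primary analysis receives.** Follow-up contacts are at day 21 ± 3, 42 ± 3, 90 ± 7 and 360 ± 14 (Table 1). Applying 6.6.3 and then 9.9:

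| Time of recurrence | Week 6 | Week 3 | Month 3 | Value used as the 6-week result |
|---|---|---|---|---|
| Before the week-3 call | not collected | not collected | not collected | none after baseline |
| Between the week-3 and week-6 calls | not collected | collected before recurrence | not collected | pre-recurrence week-3 score |
| After an early week-6 call (day 39 to 41) but within 6 weeks | collected | collected | not collected | week-6 score; later data lost |

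In the first two rows no post-recurrence score exists. The 9.9 sensitivity analysis compares a data set with the pre-recurrence substitute against one with nothing. Neither contains the recurrence, so agreement between them would not be reassuring.

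**2. Could identification depend on arm?** Section 6.2 leaves allocation open to participants and site coordinators, and 6.6.4 limits blinding to the week-6 evaluators and the statistical analyses. As 6.6.3 names no assessor, arm-dependent reporting or classification is possible.

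**3. Is there a planned figure to reproduce?** There is none for recurrence. The nearest is the 15% drop-out allowance in 9.4: 156 / 0.85 = 183.5, rounded up to 184, which reproduces. That allowance protects the number analysed, not the comparability of the arms.

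**4. Illustration of size.** Both inputs are assumptions: the between-arm difference in recurrence rate, and the score excess D in those who recur.

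Simple form, shift = difference in rate × D:
- low: 0.02 × 10 = 0.2 points, and 0.2 / 3 = 7% of the pass criterion;
- high: 0.04 × 15 = 0.6 points, and 0.6 / 3 = 20%.

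At a 5% rate overall, 0.05 × 184 = 9.2, so about 9 participants are affected.

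Mixture form. Let retained means be 9 (tool) and 12 (control), a difference of −3, and let those who recur score 12 + D in either arm. With recurrence rates pT (tool) and pC (control):

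full difference = [(1 − pT) × 9 + pT × (12 + D)] − [(1 − pC) × 12 + pC × (12 + D)] = −3 + 3pT + (pT − pC) × D

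| pT | pC | D | Full difference | Shift from −3 |
|---|---|---|---|---|
| 2% | 2% | any | −2.94 | 0.06 |
| 5% | 5% | any | −2.85 | 0.15 |
| 5% | 2% | 5 to 15 | −2.70 to −2.40 | 0.30 to 0.60 |
| 10% | 5% | 5 to 15 | −2.45 to −1.95 | 0.55 to 1.05 |
| 5% | 10% | 5 to 15 | −3.10 to −3.60 | −0.10 to −0.60 |

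The sign depends on which arm has more recurrences. Both forms treat everyone who recurs as omitted. For given inputs they are therefore upper figures, provided that the substituted week-3 scores recover some of the excess rather than falling below the retained week-6 mean.

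**The case against.** The case for leaving the rule alone has several parts.

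- **A recurrence is a new episode.** One may want the effect on the index episode only. The protocol never states that target, though, and 9.1 points the other way. Collecting the data permits both analyses; stopping permits one.
- **Nobody is excluded from the cohort.** This stands. A reader might infer that the primary comparison becomes one among participants without recurrence. The text does not say so: later recurrences stay in with a week-3 score, and only recurrence before the week-3 call leaves no post-baseline value. The fault is missing and substituted outcomes, not a restricted analysis set.
- **Unblinded identification is not stated.** This also stands. A reader might infer that recurrence is judged by staff who know the allocation; 6.2 and 6.6.4 make that plausible but do not say it. AVS at entry requires documented nystagmus (6.6.1), an objective element that, if also applied to recurrences, would limit arm-dependent labelling.
- **No effect of the tool on recurrence is claimed.** Correct: the documents do not say that rehabilitation changes recurrence. With equal rates the shift is 0.06 points at 2% and 0.15 at 5%, and the 1.05-point extreme needs 10% against 5% with a 15-point excess.
- **Recruitment was well advanced.** Section 9.6 reports 138 included on 25 April 2023, of whom 129 had reached 6 weeks. This limits what an amendment can gain but does not defend the rule.

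**Conclusion.** The conflict in the text is clear: the stop in 6.6.3 cannot be squared with 9.1, with the stated purpose of 9.9, or with the rule in 6.6.3 for participants who cannot train. Followed as written, it can bias the primary result, and the loss cannot be undone in analysis.

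The size and direction of bias cannot be established from the protocol. The 0.2 to 0.6 points rest wholly on assumed rates and score excesses and treat every recurrence as omitted. If recurrence is rare and balanced, the effect is minor.

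Two further readings go too far. One is that the rule is shown to favour the tool; nothing in the protocol fixes the sign. The other is that the falls endpoint loses those most at risk; no section links recurrence to falls. What can be said is that falls and fractures after the stop go unrecorded for these participants.

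**What to change.** Amend 6.6.3 so that recurrence does not end data collection:

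- record the date of recurrence and state who determines it;
- keep the blinded week-6 VSS-SF call, the 3-month and 12-month contacts, and falls and fracture recording;
- analyse all randomised participants in their assigned arm;
- report recurrence by arm;
- use exclusion of recurrences only as a sensitivity analysis.

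Whether training continues after a recurrence is a clinical matter and is not addressed here. A participant's right to withdraw is unaffected.

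Cost: the contacts are already scheduled, but the amendment may need approval by the ethics authority and the medical products agency before use (section 11). It reaches only those still to be enrolled or followed. On the 9.6 figures that was 184 − 138 = 46 not yet included (25%), plus 138 − 129 = 9 not yet at 6 weeks on that date. The trial would then contain two follow-up rules, which should be reported. For earlier recurrences, report the number by arm and, where consent allows, attempt the remaining scheduled contacts.

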#### 6.6.4. Unblinding

The clinical investigation is only blinded for the evaluators at week 6 and for the statistical analyses. Therefore, no emergency code breaking protocol is needed.

### 6.7. Procedures

**Figure 1. Study outline – Internet-based vestibular rehabilitation versus standard care after acute onset vertigo, a randomized controlled trial**

[figure not shown]

VSS-SF – vertigo symptom scale short form. vHIT – video head impulse test. EQ-5D – EuroQol five-dimension scale. DHI – dizziness handicap inventory. T25-FW – timed 25-foot walk test. BPPV – benign paroxysmal positional vertigo. q – questions, t – testing.

Eligible patients will be identified by the site study coordinator using daily emergency department, medical/neurological and ENT wards vigilance (contacting the on-call doctors, contacting the emergency department staff, manual patient list screening including screening of the relevant wards, notice-board ads and information brochures at each department and ward). ENT outpatient clinics identify eligible patients from subacute AVS visits. Local variations of these methods to identify eligible patients will be put in place by each site PI. Eligible patients are screened for participation with a screening checklist (inclusion/exclusion criteria) including screening for nystagmus using videofrenzel goggles (screening of eye movements looking straight forward, 30 degrees to the right, 30 degrees to the left, up, and down); the presence of nystagmus must be documented to be present at least 24 hours after symptom debut.

Subjects will be randomized to the intervention group or control group as detailed in section 6.2.

**Intervention:** Online 6 weeks vestibular rehabilitation demanding 15–20 minutes of training each day. The intervention aims at maximizing central compensation for the vestibular/balance deficit. It consists of weekly online sessions and daily exercises. The

weekly online sessions consist of educational texts, symptom control techniques, scoring tests and exercise prescriptions for the following week. The exercises for the following week after each online session will be adapted to the user and thus become successively more difficult if the user scores lower discomfort during evaluations, or the opposite if the user scores higher discomfort. There are 6 different exercises in the tool: 1. Head shake with open eyes, gaze following the head; 2. Head nod with open eyes, gaze following the head; 3. Head shake with closed eyes; 4. Head nod with closed eyes; 5. Head shake with open eyes, gaze fixated and; 6. Head nod with open eyes, gaze fixated. These exercises are performed sitting, standing and walking depending on symptom intensity. There are 4 symptom control techniques in the tool in order to deal with secondary anxiety issues related to the vertigo: 1. Controlled breathing; 2. Relaxation; 3. Stress management and; 4. Thought control.

Control: After randomization written instructions with the 6 different exercises from the online rehabilitation tool is handed out and the participant is instructed to increase difficulty if possible. Participants are also given general advice to prevent inactivity and secondary dizziness and fear of motion. Data collection as for the intervention arm. At the end of the core study at 3 months from randomization the standard care study arm participants will also be granted access to the online rehabilitation tool and followed until 12 months.

The Swedish translations of VSS-SF, DHI, and EQ-5D-3L are collected locally at all sites by the site study coordinator. These questionnaire data will be collected by in-person interview at day 0, week 6 and after 3 months, except for VSS-SF at 6 weeks (primary endpoint) which will be collected by phone call interview by a blinded study coordinator at either the same site or a different site. In the case of the first 100 included subjects, the VSS-SF at 6 weeks (primary endpoint) will be collected by phone call interview twice, 48 hours apart, as part of the statistical validation of the Swedish translation of the VSS-SF questionnaire. Also, at week 3 and after 12 months VSS-SF and EQ-5D data will be collected by phone call interview (figure 1).

The T25-FW data will be collected by letting the subject walk a clearly marked 25-foot course during follow-up appointments at each site.

Basic body sway data will be collected by each site study coordinator using a locally developed application which utilizes cell phone built-in motion tracking. An enhanced gait analysis with a wearable motion tracking system will be performed at Umeå University Hospital for in-depth measurements.

The participants will be instructed to keep a provided pedometer on them as often as possible during the first 3 months. The total number of steps for the first 6 weeks, and from week 6 to 3 months will be recorded into REDCap will be compared between the study arms at week 6 and after 3 months.

At sites with access to vHIT we will also measure VOR gain and catch-up saccades by performing vHIT at day 0, 6 weeks and 3 months.

The catch-up saccades (yes/no, proportion of impulses with saccades) will also be compared between the study arms at 6 weeks and 3 months (affected side).

The 12 months data collection to capture potential long-term effects of early intervention will be performed by the Umeå University Hospital study coordinator by contacting all participants by telephone at 12 months after inclusion. During this phone call one last round of VSS-SF questionnaire data will be collected (Figure 1).

